#### Usual care

Patients assigned to the usual care arm complete the same baseline interviews and follow-up as intervention patients. If requested by the admitting team or oncologist of record, usual care patients may also receive a palliative care consultation.

### Outcome measures

Outcomes were specified ahead of time, and include the rate and timing of palliative care consultation, quality of life and depression at 12 weeks, health care utilization, and survival. Independent variables are collected via a baseline interview with the patient or obtained from the electronic medical record, and are listed in Table 2. Dependent variables are listed in Table 3. The primary outcomes include rate and timing of palliative care consultation, quality of life and depression at 12 weeks, hospital length of stay, and survival. Secondary outcomes include costs during the index admission, ICU admission and ICU days, and ED revisits and re-hospitalization at 30 and 180 days. Objective outcomes were chosen that could be obtained from a chart or administrative data review to eliminate the possibility of recall bias or differential follow-up rates between the intervention and care-as-usual group.

**Table 2 T2:** Independent variables

**Variable**	**Measurement**	**Source**
Treatment group	Intervention, usual care	Research coordinator
Primary MD status	Full-time faculty/hospitalist, voluntary/private practice	Medical Record
Primary MD specialty	Heme/Onc, general medicine, other	Medical Record
Age	Years	Medical Record
Gender	Female, Male	Medical Record
Race/Ethnicity	Asian, Black, Hispanic Black, Hispanic White, Native American, White, Other	Patient Interview
Religion	Catholic, Protestant, Jewish, Muslim, Buddhist, Other, None	Patient Interview
Cancer diagnosis	Tumor type and stage	Medical Record
Performance status	ECOG Performance Status	Patient Interview
Medical comorbidities	Charlson co-morbidity index	Medical Record
Prior living situation	Home, nursing home, hospice	Patient Interview
Use of formal home care	Yes/no, Type of services, h/week	Patient Interview
Primary caregiver	Name and relationship/none	Patient Interview
Advance directives	Living will, health care proxy, power of attorney for health care/none	Patient Interview
Medical insurance	Medicare, Medicaid, Medicaid/Medicare managed care, Medicare managed care, traditional indemnity, self-pay, other	Administrative database, Medical Record

**Table 3 T3:** Dependent variables

**Variable**	**Measurement/Instrument**	**Source**

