**Primary Dependent Variables**		
Rate and timing of palliative care consultation	Yes/No; Days from enrollment to consultation	Medical Record
Quality of life	FACT-G at 12 weeks	Patient Interview
Depression	PHQ-9 at 12 weeks	Patient Interview
Hospital length of stay	Days during index admission	Medical Record
Survival	Days from enrollment	Medical Record

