### Analysis

We estimated our sample size based on one of our primary outcomes (time to palliative care) by utilizing data from the palliative care database on consultation in patients with advanced cancer. The baseline mean time to consultation for such patients seen by palliative care was 9 days (SD = 12). We estimated that our intervention would decrease this number by at least 50%, to 4.5 days (estimated SD = 6 days). Calculations employ two-tailed tests (α = 0.05, with β = 0.80). We plan to enroll and randomize at least 140 patients. We expect to have at least 80% power with α = 0.05 (two-sided) to detect clinically meaningful differences in these primary outcome variables with 70 subjects/group.

The primary analysis will be a traditional intention-to-treat that will compare intervention to control subjects on our predetermined primary and secondary outcomes. Two sample *t*-tests, Mann–Whitney, or *χ*^2^ will be used as appropriate depending on whether the outcome is continuous or discrete, and whether it is normally distributed. For the quality of life data, where there is a baseline score, ANCOVA will be used to compare outcomes between the two groups, and patients who die will be excluded from this analysis. A series of secondary analyses will be conducted if there is significant contamination between the intervention and control group. In the first of these sets of analyses, randomization assignment will serve as an instrumental variable and percentage of admissions receiving palliative care will be included as a covariate. We will also compare primary and secondary outcomes per protocol (i.e., patients will be grouped according to whether they received a consultation, rather than on their randomization scheme). We expect outliers in our outcome data and will not be excluding them from the analysis. Because of the small sample size, we will not account for permuted blocked randomization in the analyses.

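### Six unranked primary outcomes share one power claim at two-sided 0.05; two largely measure delivery, and the other four carry a 16% to 19% chance of a false positive.

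*Protocol article*

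**What the plan says.** Under Outcome measures the protocol article writes: "The primary outcomes include rate and timing of palliative care consultation, quality of life and depression at 12 weeks, hospital length of stay, and survival". Table 3 repeats the list and records consultation as two measurements, "Yes/No; Days from enrollment to consultation". Five table rows therefore give six outcomes: consultation rate, consultation timing, FACT-G, PHQ-9, length of stay and survival. None is placed above another.

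The Analysis section bases the sample size on time to consultation, described as one of several primary outcomes, and gives means and standard deviations for that outcome only. It then claims at least 80% power at two-sided α = 0.05 "to detect clinically meaningful differences in these primary outcome variables with 70 subjects/group". The intention-to-treat analysis will "compare intervention to control subjects on our predetermined primary and secondary outcomes".

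Intervention arm says that assigned patients receive the palliative care consultation the same or the following day. Usual care says that control patients may receive one if the admitting team or oncologist asks. The Abstract, Design and Discussion call the trial a pilot that will give preliminary estimates for a larger study.

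**The concern.** Two different problems sit under one label.

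First, the outcomes called primary differ in kind. Consultation rate and timing are moved directly by paging the palliative care team, which is what the intervention arm consists of. Quality of life, depression, length of stay and survival are what the consultation is hoped to change. With all six equally primary, a difference in delivery could be reported as success on a primary outcome even if no patient did better.

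Second, the four remaining outcomes each offer a separate chance of a false positive. The only error level in the article is 0.05, and it is attached to the primary outcomes in the plural. If each is read at that level, the chance that at least one crosses it by luck is well above 5%.

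The power statement adds to both problems. It covers the whole primary set, but the article supports it for one member only, so a reader may take a null result on survival or quality of life as coming from an adequately powered comparison.

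**Working it through.** **1. Reproduce the stated sample size.** Inputs, all from Analysis: control mean 9 days (SD 12), intervention mean 4.5 days (SD 6), two-sided α = 0.05, power 80%. The text prints β = 0.80; I read it as power, as the later sentence does.

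n per group = (SD₁² + SD₂²)(z₀.₉₇₅ + z₀.₈₀)² / difference²
= (144 + 36)(1.960 + 0.842)² / 4.5²
= 180 × 7.849 / 20.25 = 69.8, rounded up to 70.

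Power at 70 per group: standard error = √(180/70) = 1.604; 4.5/1.604 = 2.806; Φ(2.806 − 1.960) = 80.1%. A Welch t-test gives 79.4%. The stated 70 per group, 140 in total, therefore reproduces for time to consultation at the full 0.05. No effect size or variability is given for the other five primary outcomes, so the claim cannot be checked for them.

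**2. False-positive chance for the four patient outcomes.** With k independent tests at 0.05 and every null hypothesis true, the chance of at least one false positive is 1 − 0.95^k.

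k = 4: 1 − 0.95⁴ = 1 − 0.8145 = 18.5%.

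The document gives no correlations, so dependence is an assumption. Simulating four equicorrelated normal test statistics (1,000,000 draws, two-sided 0.05 each):

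| Assumed common correlation | At least one false positive, four outcomes |
|---|---|
| 0 (exact) | 18.5% |
| 0.3 | 17.4% |
| 0.5 | 15.6% |
| 0.7 | 13.0% |

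Between independence and correlation 0.5, the chance is three or more times the nominal 5%.

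**3. What a correction would cost.**

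- *Across all six.* At the strictest Holm step, 0.05/6 = 0.00833, the critical value is 2.638. Power for time to consultation at 70 per group becomes Φ(2.806 − 2.638) = 56.7%. Restoring 80% needs 180 × (2.638 + 0.842)² / 20.25 = 107.6, so 108 per group or 216 in total.
- *Across the four patient outcomes only.* The first step is 0.05/4 = 0.0125, critical value 2.498. An outcome with exactly 80% power at 0.05 has an expected test statistic of 1.960 + 0.842 = 2.802, so its power at that step is Φ(2.802 − 2.498) = 61.9%. This is illustrative, because the article does not establish that any of the four has 80% power at 0.05.
- *One primary outcome, time to consultation.* The level stays at 0.05, and 70 per group with 80.1% power is unchanged.

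**The case against.** Four points can fairly be made for the plan.

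*It is a pilot.* The stated purpose is feasibility and preliminary estimates, and no rule says that one significant outcome makes the trial positive. Family-wise error matters most where a single result carries a confirmatory claim. This stands in part: it lowers the consequence. It does not remove it, because the Analysis section plans formal tests, claims power for the set, and the Discussion states directional hypotheses for these outcomes.

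*The 0.05 appears only in the sample-size text, and an unseen analysis plan may control multiplicity.* Also partly right: the article sets no separate testing level, and the absence of a correction is not itself the finding. But naming the primary outcomes is a choice that this document has already made, and the power claim at 0.05 for all of them is in print. An equal split of 0.05 over the six would not fit 70 per group, as the 56.7% shows.

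*Rate and timing are legitimate outcomes.* They are. The intervention is a referral from the emergency department, and the Discussion hypothesises an effect on both. The objection is only to giving them the same standing as patient outcomes. Nor is a significant difference assured: usual-care patients can be consulted and contamination is foreseen. Likely is as far as the text goes.

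*The size of the error.* A reader might infer a false-positive chance of 21% to 26% by counting all six outcomes (26.5% if independent, 20.7% at correlation 0.5). That arithmetic is correct for six true null hypotheses, but the nulls for rate and timing are not credible when one arm is referred by design. The document supports a count of four.

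**Conclusion.** The point holds as a fault in how the primary outcomes are set. Six are named without rank, the power claim extends to all of them, and only time to consultation has figures behind it. A significant result on consultation rate or timing is likely and would say little about benefit to patients.

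For the four patient outcomes, the chance of at least one false positive is about 16% to 19%. This rests on three assumptions: each is judged at 0.05, the only level the article gives; there is no true effect on any of the four; and their common correlation lies between 0 and 0.5. Stronger correlation lowers the figure, to 13.0% at 0.7.

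The text does not support saying that the trial will declare success on any one outcome. It leaves that reading open, which is reason enough to amend the wording but not a fatal flaw in a pilot.

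**What to change.** 1. Name time to consultation, the outcome that the trial was sized on, as the single formally tested primary outcome at two-sided 0.05. State that it is a process outcome and cannot by itself support a claim of patient benefit.
2. Confine the 80% power statement to that outcome.
3. Report consultation rate, FACT-G, PHQ-9, length of stay and survival as secondary estimates with 95% confidence intervals and no significance claim. This matches the stated aim of preliminary estimates.
4. If a significance claim on the patient outcomes is wanted, apply Holm across FACT-G, PHQ-9, length of stay and survival at a family-wise 0.05, and state the loss of power.

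Items 1 to 3 need only a change of wording. The sample size stays at 70 per group, and since the trial was still enrolling at submission, the change can be made before analysis. Moving timing out of the primary position instead would leave the 140 without its only stated basis. The price of items 1 to 3 is that fewer outcomes can be declared significant. Item 4 also costs power: an outcome with 80% power at 0.05 has about 62% at the first Holm step.

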**Primary Dependent Variables**		
Rate and timing of palliative care consultation	Yes/No; Days from enrollment to consultation	Medical Record
Quality of life	FACT-G at 12 weeks	Patient Interview
Depression	PHQ-9 at 12 weeks	Patient Interview
Hospital length of stay	Days during index admission	Medical Record
Survival	Days from enrollment	Medical Record
**Secondary Dependent Variables**		
ICU Admission and ICU length of stay (if admitted)	Yes/No; ICU bed days	Administrative database
Hospital costs	Total, direct costs during index hospitalization	Administrative database
Hospital readmissions over 30 and 180 days from enrollment	Count	Medical Record
Repeat ED visits over 30 and 180 days from enrollment	Count	Medical Record

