### Data collection and management

After the patient is determined to meet inclusion criteria and provides consent, the face-to-face survey is administered in English or Spanish in the ED and takes approximately 15 minutes, depending on responses and interruptions. Research assistants are trained to understand that data collection never interferes with medical care and the interview is stopped for any reason related to their care. The research assistant administers the baseline survey electronically on a table computer using Survey Monkey, an online survey tool. All protected health information is entered into a separate encrypted, password-protected database with only a unique linking identification number to match this information with that entered in Survey Monkey.

The survey includes questions regarding demographics, including gender, race/ethnicity, marital status, income, education, religious affiliation, type of residence, history of an advance directive or designation of a health care proxy, and health insurance; functional status is measured using the Eastern Oncology Cooperative Group score [8]; quality of life measured using the Functional Assessment of Cancer Therapy-General Measure [9]; and the Patient Health Questionnaire-9 [10] is used to screen for depression. Quality of life and depression are measured again at 6 and 12 weeks. The 6-week measurement was added one month into the protocol because a large proportion of our first participants died before the 12-week follow-up.

Six months after the ED visit, outcome data is collected via the electronic medical record and administrative data review using the *Mount Sinai Data Warehouse*. It provides content such as registration data, lab results, medications, radiology reports, procedures, and billing information. For the chart and administrative data review, a codebook was developed, inter-rater reliability was measured, and the research assistant performing chart abstraction was blinded to patient assignment.

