## Discussion

Here, we describe the design of a clinical trial to determine the impact of a palliative care intervention for advanced cancer patients in the ED on quality of life, depression, health care utilization, and survival. While this is a pilot trial to establish feasibility, it will provide an estimate of the effect of the intervention on our predetermined outcomes that can be used to inform the design of a larger multicenter trial.

Systematic reviews of palliative care have concluded that trials are sparse and findings limited due to methodological shortcomings inherent to this patient population [11]. Only a small proportion of the research in palliative care is based on clinical trials [12], as recruitment and retention of these patients for palliative care studies have proven challenging [13]. The ED setting adds other unique challenges not encountered in other settings. The environment is crowded and chaotic, and there is little privacy. Patients often have a high symptom burden and are in significant distress, all of which can preclude participation in research. The specificity of our environment, coupled with the lack of published clinical trials in palliative care, make the publication of our study protocol especially important to further research in this arena.

Visits to the ED for patients with advanced cancer are common, demonstrating the potential for altering the clinical course of these patients in this setting [14,15]. Despite this, there has been almost no needs-based research in palliative care and emergency medicine, and until recently little emphasis has been placed on education, research, or practice guidelines in end-of-life or palliative care in this important setting [16]. While some EDs are pilot testing palliative care programs, there has not been a structured and rigorous approach to the development and testing of such interventions to assure their success and test their impact on predetermined outcomes.

We hypothesize that ED-initiated palliative care consultation will increase the rate and decrease time to palliative care consultation, improve quality of physical and mental health, decrease health care utilization, and may even increase survival. We believe that it is not only feasible to enroll ED patients with serious illness in trials of palliative care, but that the ED presents a unique window in which to do so.

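### The 180-day readmission and ED-visit counts take no account of days alive, and ICU days may be compared only among ICU patients, in a trial with high early mortality

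*Protocol article*

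**What the plan says.** Table 3 lists two secondary outcomes measured as counts: "Hospital readmissions over 30 and 180 days from enrollment" and "Repeat ED visits over 30 and 180 days from enrollment". A third secondary row reads "ICU Admission and ICU length of stay (if admitted" and closes its bracket there; it is measured as yes/no and as ICU bed days. Hospital length of stay, a primary outcome, is "Days during index admission". Survival, also primary, is recorded in days from enrollment.

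The Analysis section applies t-tests, Mann–Whitney or chi-square tests, which "will be used as appropriate depending on whether the outcome is continuous or discrete" and on normality. Its one rule on death belongs to the quality-of-life ANCOVA: "patients who die will be excluded from this analysis".

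Two other sections matter. Data collection and management explains the added 6-week measurement by saying that "a large proportion of our first participants died before the 12-week follow-up". The Discussion expects the intervention to "decrease health care utilization, and may even increase survival".

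**The concern.** A patient who has died can no longer be readmitted or return to the ED. With many early deaths, a large part of the sample cannot contribute 180 days. If the intervention lengthens life, its patients have more days in which events can occur, so the two hoped-for effects (less use, longer survival) pull the same count in opposite directions. If it shortened life, the count would fall and look like a benefit.

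The Outcome measures section justifies chart-based outcomes partly because they avoid unequal follow-up between the arms. That does not hold for counts cut short by death when survival differs.

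ICU days among those admitted to ICU raise a separate problem. Admission to ICU happens after randomisation and may be affected by the intervention, so the two ICU subsets need not be comparable.

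At stake are secondary outcomes, and the reading of one primary outcome (length of stay), within one of the three components of the second aim. The Discussion says that the estimates will inform a larger multicenter trial, so a misread direction could be carried forward.

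**Working it through.** **The plan's own figure.** The article gives no sample size or expected value for any utilisation outcome. Its only calculation is for time to consultation: means 9 and 4.5 days, SDs 12 and 6. With SD = √((12² + 6²)/2) = 9.49, two-sided α = 0.05 and 80% power, this gives 70 per group, as stated. It has no bearing on this point.

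**Inputs for the counts.** From the article: windows of 30 and 180 days from enrollment, 70 patients per group, and high mortality before week 12 with no figure. Assumed: a share p of controls dead by day 84 of 30% to 60%, exponential survival, a mortality hazard ratio (HR) of 0.6 to 0.8, and a constant event rate per day alive.

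**Formulas.** Control hazard h = −ln(1 − p)/84; intervention hazard h × HR. Mean days alive to day T = (1 − e^(−hT))/h. With equal event rates, the ratio of mean counts equals the ratio of mean days alive.

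**One case in full: p = 50%, HR = 0.7, T = 180.**
- Control: h = 0.6931/84 = 0.00825; mean days alive = (1 − 0.2264)/0.00825 = 93.7.
- Intervention: 0.7 × 0.00825 = 0.00578; mean days alive = (1 − 0.3536)/0.00578 = 111.9.
- Ratio 111.9/93.7 = 1.19: a 19% higher raw count with no difference in rate.
- With 0.01 events per day alive in controls and a true 10% lower rate in the intervention arm, the raw means are 0.01 × 93.7 = 0.94 and 0.009 × 111.9 = 1.01. The sign reverses. Events per day alive would show 0.009/0.010 = 0.90.

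**Range: intervention/control ratio of raw 180-day counts at equal rates.**

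| Controls dead by week 12 | HR 0.6 | HR 0.7 | HR 0.8 |
|---|---|---|---|
| 30% | 1.147 | 1.108 | 1.070 |
| 40% | 1.206 | 1.149 | 1.096 |
| 50% | 1.271 | 1.194 | 1.123 |
| 60% | 1.342 | 1.241 | 1.152 |

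The excess is 7% to 34%. A true rate reduction of 1 − 1/1.070 = 6.5% up to 1 − 1/1.342 = 25.5% would be fully hidden. A 10% reduction changes sign wherever the ratio exceeds 1/0.9 = 1.111, which is 9 of the 12 cells. At 30 days the ratios run only from 1.013 to 1.065.

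**Effect on the test.** In 3,000 simulated trials of 70 per group (p = 50%, HR = 0.7, equal event rates), Mann–Whitney gave p < 0.05 in 15%, almost always with more use in the intervention arm. With equal survival the figure was 5%.

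**ICU days (invented numbers, to show the mechanism).** Control: 20 of 70 admitted to ICU, 4 days each. Intervention: 10 of 70, 6 days each. Among those admitted the intervention looks worse, 6 against 4 days. Per randomised patient it looks better: 10 × 6/70 = 0.86 against 20 × 4/70 = 1.14.

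**Length of stay (invented numbers).** Take 10 days if discharged alive and 4 if the patient dies in hospital. Raising in-hospital death from 10% to 20% lowers the mean from 0.9 × 10 + 0.1 × 4 = 9.4 to 0.8 × 10 + 0.2 × 4 = 8.8 days. Mean stay alone cannot show why it fell.

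**The case against.** The strongest reply is that a count over a fixed window in all randomised patients is a legitimate intention-to-treat quantity: total use per patient enrolled. Survival is a primary outcome and will be reported beside it. This stands, and it is why the raw counts should be kept. The simulated 15% is likewise not a false-positive rate for total use; it is misleading only when read as a difference in the rate of use. The plan nevertheless offers no analysis that separates fewer events from fewer days alive.

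On ICU days, the bracketed condition may only say when the field is filled in. Outcome measures lists ICU days without it, and the Analysis section promises intention-to-treat. ICU admission yes/no is also an outcome for everyone, so only ICU days are affected. The comparison among ICU patients is therefore a plausible reading that the text does not fix.

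A reader might infer that the plan scores an in-hospital death as a favourable short stay. The article states no such rule. It counts index days and is silent on these deaths, a detail that a full analysis plan may settle. A reader might also infer that a shorter index stay noticeably inflates 30-day readmissions. The article gives no length of stay (its 9 days is time to consultation), so that effect cannot be sized from it.

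Finally, an unseen analysis plan could add a rule for the counts. But the article itself fixes their definition and the tests, and it considers death elsewhere, so this is more than an omission.

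**Conclusion.** The point holds for the 180-day counts, and for ICU days if they are compared among ICU patients only. At equal event rates the longer-surviving arm shows 7% to 34% more events by day 180. At 30 days the excess is 1.3% to 6.5%, too little to matter much.

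These sizes rest on assumed mortality, an assumed survival benefit, exponential survival and a constant event rate per day alive. If use clusters shortly before death, the size would differ. With equal survival the distortion disappears.

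A reader might conclude that the utilisation results will point the wrong way. The documents do not support that: reversal needs a survival difference large enough to outweigh the difference in rate, and nothing shows that this will occur. For length of stay, the conclusion is only that in-hospital death should be reported with it.

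**What to change.** 1. Keep the raw 30- and 180-day counts and label them total use per randomised patient.
2. Add a comparison of events per day alive from enrollment in all randomised patients, for example negative binomial regression with log days alive, capped at 30 or 180, as the offset. Count the enrollment day as day 1 so that the offset is always defined. Interpret the result beside survival. Starting at enrollment rather than at index discharge keeps patients who die during the index stay in the analysis.
3. Compare ICU days in all randomised patients, with zero for those not admitted to ICU.
4. Report in-hospital death by arm beside index length of stay.
5. Optionally add days alive and out of hospital to day 180. This needs readmission bed-days, which Table 3 does not list, so first check that the data warehouse can supply them.

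Items 2 and 3 use survival days and ICU days that the trial already collects; item 4 needs only vital status at the end of the index stay. No further patient contact is needed, and the article says that the trial is still enrolling, so the wording can be settled before analysis. The cost is slightly more analysis work, and the rates are less directly comparable with studies that report raw counts.
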